The present prospective POLCAR trial investigates whether the results of the previous prospective trial can be generalized to elderly patients aged ≥65 years [6]. Its major goal is the identification of the optimal cut-off score to correctly diagnose pneumonitis and discriminate it from other lung diseases in elderly patients irradiated for lung cancer. In addition, the diagnostic value of an increase in the scoring points from baseline scores is evaluated. This study is a prerequisite for the development of a mobile application that can be used by patients at home to rate their symptoms possibly related to pneumonitis. This information will contribute to the decision whether pneumonitis is possible or likely and whether consultation of a pulmonologist or presentation to a hospital is required. This article reports on the study protocol of the POLCAR trial, including the objectives of the study, the eligibility criteria, planned assessments, interventions, information regarding sample size calculations, and the statistical methods used for primary and secondary outcomes.

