If the total score is higher than at baseline prior to the start of radiotherapy, the patients receive a follow-up call after 3 days or are asked to present at the corresponding hospital. If pneumonitis is suspected, the patients undergo lung function tests. The suspected diagnosis of pneumonitis is considered substantiated in case of a decrease in forced expiratory volume in 1 s (FEV1) and diffusing capacity of the lung for carbon monoxide (DLCO) to less than 75% from baseline values [16,17]. In this situation, the patients receive a chest X-Ray (which may be supplemented by a computed tomography). Radiation pneumonitis is considered confirmed if opacities confined to the irradiation fields are seen on chest X-Ray and/or ground-glass opacities (focal or nodular), consolidation, or both are seen on computed tomography [18,19]. The imaging findings are interpreted by experienced radiologists. If the diagnosis of pneumonitis grade ≥ 2 (CTCAE v5.0) is made, the patients generally receive treatment with prednisolone [5,16,20]. If the symptoms are caused by a medical condition other than pneumonitis, the patients are treated for this situation. Finally, the total score of the symptom-based scoring system is correlated to pneumonitis (yes or no). Since the scoring tool is easy to use, consistent assessment across multiple centers appears secured. This assumption is supported by the experiences from a previous prospective trial [6].

At the end of the radiotherapy course, the patients will complete a questionnaire regarding their satisfaction with the paper-based version of the scoring system, modified according to the User Experience Questionnaire, a widely used and reliable tool [21,22]. If the dissatisfaction rate is >20%, the scoring system needs to be modified, and if the dissatisfaction rate is >40%, it is considered not useful. If patients withdraw their consent to participate in the trial, study-specific interventions are stopped. In case of adverse events, which do not allow patients to complete subsequent questionnaires, study-specific interventions are postponed or discontinued, if necessary.

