Due to the limited sample size that could be realistically achieved in this multi-center trial within the given study duration, it was not considered feasible to develop and validate the optimal cut-off value identified within this single study at the same time by dividing the study population into training and validation cohorts. Therefore, the derived cut-off value should be considered a preliminary suggestion, which should be validated in subsequent studies. As a further sensitivity analysis, the relationship between tertiles of the symptom-based scores and the incidence of radiation pneumonitis will be statistically tested using the Jonckheere–Terpstra test, which is a nonparametric test for ordered differences among groups of score values [27,28,29]. It tests the global null hypothesis that the distribution of the response variable does not differ among tertiles. The test is designed to detect alternatives of ordered differences, meaning that the incidence of pneumonitis increases with the tertiles of score values. In addition, the impact of potential risk factors, including radiation dose, co-morbidity (particularly significant cardiovascular disease), history of smoking, radiation doses, and concurrent medication including chemotherapy and immunotherapy on the prevalence of pneumonitis, will be evaluated [4]. The histology of lung cancer (NSCLC or SCLC) was not associated with pneumonitis in previous studies and, therefore, its potential impact will not be separately analyzed [4,6,14].

Based on the participation of highly committed study sites only and our previous trial experience, the rate of missing data can be assumed to be rather low. Furthermore, the primary endpoint consists of the derivation of one patient-specific value from the multiple score values documented during each visit. Based on the scientific question of interest in this single-arm trial, missing values will not be imputed regardless of any intercurrent events (“treatment policy strategy”).

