## Figures and Tables

**Table 1 cancers-17-00807-t001:** Inclusion and exclusion criteria.

Inclusion criteria Histologically proven lung cancer Indication for radiotherapy or chemoradiation Mean radiation dose to ipsilateral lung >13 Gy Age ≥65 years Written informed consent Capacity of the patient to contract
Exclusion criteria Expected non-compliance Baseline score of >4 points, as these patients will likely not be able to tolerate the planned treatment, including the full radiation dose

**Table 2 cancers-17-00807-t002:** Schedule of enrolment, interventions, and assessments.

	Screening	Baseline	Weekly During RT	End of RT	Weekly Up to 24 Weeks After RT	End of Study
Informed consent and patient information	X					
Inclusion criteria	X					
Exclusion criteria	X					
Demographics	X					
Medical history and concomitant diseases		X	X	X	X	X
Concomitant medication		X	X	X	X	X
Systemic anticancer treatment		X	X	X	X	X
Physical examination		X				X
Telephone visits					X	
Performance status		X				
Pathology and tumor stage		X				
Upfront surgery		X				
Planned treatment		X				
Lung function test		X	X ^a^	X	X ^a^	X
Chest X-Ray and blood samples (inflammation parameters) ^b^			X ^b^	X ^b^	X ^b^	X ^b^
(Serious) adverse events			X	X	X	X
Treatment given as planned?			X	X	X	X
Symptom-based scoring system (paper version)		X	X	X	X ^c^	X
Satisfaction with the symptom-based score (paper version)				X		

RT = radiotherapy; ^a^ only in case of suspected pneumonitis; ^b^ only if the suspicions of pneumonitis are substantiated after lung function test; ^c^ by phone (telephone visit).

**Table 3 cancers-17-00807-t003:** Scoring points assigned to symptoms potentially associated with pneumonitis.

Symptom	Severity of the Symptom (as Stated by the Patients)	Points
Cough	No	0
	Yes, a little/sometimes	1
	Yes, moderate/regularly	2
	Yes, severe/permanently	3
Shortness of breath	No	0
	Yes, with intense exertion (e.g., climbing stairs)	1
	Yes, with mild exertion (e.g., walking on flat ground)	2
	Yes, at rest	3
Fever	No	0
	Yes, between 37.6 and 38.0 °C	1
	Yes, between 38.1 and 39.0 °C	2
	Yes, higher than 39.0 °C	3

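### The case definition limits X-ray findings to the irradiated fields but sets no location or cause condition for CT, so other lung disease can be labelled radiation pneumonitis

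*Protocol article*

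**What the plan says.** Section 2.4 sets out a sequence. A score above baseline leads to a further call or a hospital visit. If pneumonitis is suspected, lung function is tested, and the suspicion counts as substantiated on the following finding: "decrease in forced expiratory volume in 1 s (FEV1) and diffusing capacity of the lung for carbon monoxide (DLCO) to less than 75% from baseline". Then "the patients receive a chest X-Ray (which may be supplemented by a computed tomography"). Confirmation requires that "opacities confined to the irradiation fields are seen on chest X-Ray and/or ground-glass opacities (focal or nodular), consolidation, or both are seen on computed tomography". On who reads the images, it says: "The imaging findings are interpreted by experienced radiologists". On other causes, it says: "If the symptoms are caused by a medical condition other than pneumonitis, the patients are treated for this situation". The total score is then related to pneumonitis as yes or no.

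Table 2 schedules "Chest X-Ray and blood samples (inflammation parameters") once lung function has substantiated the suspicion. Section 2.6.1 plans to examine the effect of "concurrent medication including chemotherapy and immunotherapy on the prevalence of pneumonitis, will be evaluated", so patients may be receiving these drugs.

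The Introduction gives the main goal as finding the cut-off score to "correctly diagnose pneumonitis and discriminate it from other lung diseases in elderly patients irradiated for lung cancer", and the Conclusions repeat it. Section 2.6.2 states that predictive values can be estimated without bias because the number of cases is not fixed in advance.

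**The concern.** The two imaging routes to the same endpoint differ. The X-ray route requires opacities limited to the irradiated fields. The CT route requires only ground-glass opacity or consolidation, wherever it lies and whatever its cause. The routes are joined so that either suffices, and no condition is given for when CT is added. Case status can therefore depend on whether a site orders a CT. Five sites take part, and the Discussion accepts that local care pathways may influence results.

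The label is the reference standard for every performance measure in the trial. Infection or drug-related pneumonitis with cough, dyspnoea and fever is the kind of disease the score is meant to tell apart from radiation pneumonitis. If some of these patients are counted as cases, the trial credits the score for detecting them. The reasoning in section 2.6.2 about unbiased predictive values concerns how patients are sampled. It does not cover an error in the label.

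**Working it through.** **1. Does any written step close the gap?**

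- Lung-function criterion (section 2.4): a fall in FEV1 and DLCO, with no cause named.
- Radiologist reading (section 2.4): names the reader but gives no rule for location or cause.
- Other-condition sentence (section 2.4): concerns treatment. It also speaks of conditions other than pneumonitis, so it does not separate drug-related from radiation pneumonitis.
- Inflammation parameters (Table 2): collected, but not part of the confirmation rule.

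None adds a location or cause condition to the CT route.

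**2. The plan's own figure.** Section 2.5 requires 18 patients with and 41 without pneumonitis (AUC 0.9, lower limit 0.7, two-sided 5%, assurance 80%). Of several formulas tried, one fits: z(0.975)·SE(0.7) + z(0.8)·SE(0.9) ≤ 0.9 − 0.7. With the Hanley–McNeil variance at 18 and 41 this is 1.96 × 0.0780 + 0.84 × 0.0512 = 0.153 + 0.043 = 0.196, within 0.2. The sample size is not in question, and 18/41 serves below as the base.

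**3. Relabelling, on assumed counts.** Let k mislabelled cases score at or above the cut-off. Under section 2.6.1 a case takes its score at diagnosis and a non-case its maximum over the study. The maximum cannot be lower, so each of the k becomes a false positive:

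- sensitivity = (TP − k)/(P − k)
- specificity = TN/(N + k)
- PPV = (TP − k)/(TP + FP)

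| Assumed start | k | Sensitivity | Specificity | PPV |
|---|---|---|---|---|
| 17/18 and 33/41 | 0 | 17/18 = 94.4% | 33/41 = 80.5% | 17/25 = 68.0% |
| | 1 | 16/17 = 94.1% | 33/42 = 78.6% | 16/25 = 64.0% |
| | 3 | 14/15 = 93.3% | 33/44 = 75.0% | 14/25 = 56.0% |
| 17/18 and 36/41 | 0 | 17/18 = 94.4% | 36/41 = 87.8% | 17/22 = 77.3% |
| | 3 | 14/15 = 93.3% | 36/44 = 81.8% | 14/22 = 63.6% |

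The first start is the smallest count that reaches the 80% specificity target of section 2.6.1, so one patient is bound to cross it. From the second start, three do not.

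**4. The direction can reverse.** Suppose instead that, in the first start, the one case below the cut-off is the mislabelled one and that patient's maximum also stays below. Correct labels give sensitivity 17/17 = 100%, specificity 34/42 = 81.0% and PPV 17/25 = 68.0%. The current label would then understate sensitivity and specificity.

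**5. AUC.** Let a fraction f of labelled cases be other lung disease with AUC B against the labelled non-cases, and let true cases have AUC 0.90 against them. Observed AUC = (1 − f) × 0.90 + f × B.

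| f | B = 0.5 | B = 0.7 | B = 0.9 | B = 0.95 |
|---|---|---|---|---|
| 0.2 | 0.82 | 0.86 | 0.90 | 0.91 |
| 0.4 | 0.74 | 0.82 | 0.90 | 0.92 |

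With B near 0.9 the observed AUC does not move, so the analysis would not reveal the mislabelling. For scale, suppose three of 18 are relabelled and the score does not separate them from true cases (AUC 0.5). The AUC under correct labels is then (41 × 0.90 + 3 × 0.5)/44 = 38.4/44 = 0.873, against an observed 0.90. That is a modest change, still well above 0.7.

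**The case against.** The strongest reply is that the sentence should be read within its sequence. A case also needs a raised score, clinical suspicion, a fall in both lung-function measures and a radiologist's reading. The clause on other conditions implies that someone has attributed the cause before the yes/no label is used. The article condenses a full protocol that is not shown and cites sources for its imaging criteria, so the asymmetry may be compressed wording.

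Much of this stands. These steps may remove some mislabelled patients in practice, and how the inflammation parameters are used may fairly be left to the full protocol. The confirmation rule, however, is stated here, and it attaches the location limit to one route only. If the limit was meant for both, the sentence still needs correcting.

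A reader might infer that the rule defeats the trial's aim, or that specificity and PPV will be inflated. The documents support neither. CT is optional, the filtering steps exist, the number misclassified is unknown, and inflation requires mislabelled patients to score at or above the cut-off. Nor can one conclude that a single error would sink the 80% target, since that follows only from a start at 33/41. Section 2.6.1 already treats the cut-off as provisional and in need of validation, which limits the harm.

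**Conclusion.** The point holds as a defect in the stated endpoint definition. The X-ray and CT routes apply different conditions, and under the CT route other lung disease can be labelled radiation pneumonitis. This undermines, without defeating, the aim of separating the two, and it weakens the claim in section 2.6.2 that predictive values are unbiased.

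If mislabelled patients score at or above the cut-off, specificity and PPV are overstated. On the assumed counts above, specificity is overstated by about 2 percentage points with one such patient, and by about 5.5 to 6 points with three (from 80.5% to 75.0%, or from 87.8% to 81.8%). These starting counts and numbers of errors are assumptions. Neither the actual size nor the direction can be derived from the documents, and nothing here shows that the primary test of AUC against 0.7 would change.

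**What to change.** For endpoint classification only, leaving diagnosis and care as they are:

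- Reconcile the X-ray and CT routes so that one consistent location condition governs the trial label. Which imaging criterion applies is for the sponsor to decide.
- State that patients whose findings are attributed to another lung disease are labelled non-cases.
- Record on the eCRF whether CT findings lie within or outside the irradiated area.
- Report the ROC curve, cut-off and predictive values under both the reconciled and the current wording.

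The cost is a short change to the definition, one extra eCRF field and one repeated analysis, using images already taken. There may be slightly fewer cases, and the trial label may sometimes differ from the clinical diagnosis. A location condition does not exclude infection inside the field, which is why the attribution statement is needed as well.

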### 2.5. Sample Size Calculations

The main goal of this trial is to evaluate the usefulness of a new symptom-based scoring system with respect to the identification of elderly lung cancer patients developing pneumonitis after radiotherapy. The discriminative power of the symptom-based score will be assessed by calculating the AUC. The sample size is calculated to achieve acceptable precision in the estimation of the AUC measured by means of the 95% confidence interval by incorporating a pre-specified probability, which is referred to as assurance, of achieving the desired lower confidence limit [23].

The sample size calculations are based on a two-sided significance level of 5%, an AUC of 0.9, a pre-specified lower bound of the confidence interval of 0.7, an assurance probability of 80%, a ratio between negative and positive cases of 2.33 (70% of patients without and 30% with radiation pneumonitis). Based on these assumptions, 59 patients (18 with and 41 without radiation pneumonitis) are required within the Full Analysis Set. Assuming that 5% of patients will not qualify for the Full Analysis Set, a total of 62 patients should be enrolled. The drop-out rate includes patients who experience difficulties in completing questionnaires due to neurocognitive decline during the study period. The Full Analysis Set includes all the subjects who started radiotherapy.

A pneumonitis rate of 30% has been considered appropriate for the sample size calculation since, in a previous retrospective study investigating elderly patients irradiated for lung cancer, 27.3% of the patients developed pneumonitis [14]. Moreover, this rate is expected to be higher in the POLCAR trial due to the weekly assessment of pneumonitis for 24 weeks compared to the standard follow-up consisting of one visit about 6–8 weeks following radiotherapy only. All the lung cancer patients aged ≥ 65 years will be screened at each participating center. The recruitment of all 62 patients should be completed within 15 months. The treatment period will be 6–7 weeks, and the follow-up period 24 weeks. This equals a total running time for the trial of 22 months.

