### 2.4. Interventions

The patients receive the same radiotherapy or chemoradiation for lung cancer as they would have received without participation in the POLCAR trial. Radiotherapy is performed as volumetric-modulated arc therapy using conventional fractionation with doses per fraction of 2.0 Gy given five consecutive days per week and total doses ranging between 60 and 70 Gy [2]. The patients in this trial may receive any medical support required for adverse events, co-morbidities, or other conditions. Trial-specific interventions include completion of a paper-based questionnaire (symptom-based scoring system) once a week during and up to 24 weeks following radiotherapy and completion of a questionnaire rating the patient satisfaction with the symptom-based scoring system at the end of the radiotherapy course. The follow-up period of 24 weeks was chosen according to the results of previous studies showing that pneumonitis can occur up to 23 weeks following radiotherapy [4,5]. The English version of the questionnaire was properly translated into the languages of the participating centers.

The patients indicate and rate symptoms potentially caused by radiation pneumonitis, i.e., cough, dyspnea, and fever (Table 3), once a week by completing a paper-based questionnaire. During the radiotherapy course, the patients complete the questionnaire at the department of radiotherapy. After completion of radiotherapy, the information regarding the symptoms potentially related to pneumonitis will be obtained weekly by phone (to minimize hospital visits). The procedure of the telephone visits is clear, and uniformity is ensured. Support from caregivers is not allowed. Since the patients are contacted actively by staff members, the risk of loss to the follow-up is comparably low. In our previous trial, the rate of termination of follow-up due to the patient’s unavailability was 8.8% [6].

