### 2.6. Statistical Methods for Primary and Secondary Outcomes

#### 2.6.1. Primary Objective

The primary objective is to assess the performance characteristics of the symptom-based scoring system for the detection of radiation pneumonitis. An evaluation will be performed in patients available for assessment of the primary endpoint who have completed at least 10 questionnaires regarding their symptoms. To allow for patient-based analyses, the multiple score values documented for each patient over time will be reduced to one clinically relevant, patient-specific value only. Thus, for patients without radiation pneumonitis during the study, the maximum score value documented throughout the study will be used, and for patients with pneumonitis, we use the value documented at the time of diagnosis. These patient-specific values represent the fundamental units for all further statistical analyses. First of all, sensitivity and specificity will be estimated for every possible cut-off value of the symptom-based scoring system.

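### The 59 patients and 80% assurance are planned for the Full Analysis Set, but the primary AUC analysis uses a narrower set for which no loss allowance is stated

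*Protocol article*

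**What the plan says.** Section 2.5 (Sample Size Calculations) plans for "an AUC of 0.9, a pre-specified lower bound of the confidence interval of 0.7", "an assurance probability of 80"%, a two-sided 5% level and a ratio of 2.33 negatives to each positive (30% with pneumonitis). It arrives at 59 patients, 18 with and 41 without pneumonitis, and places that requirement in the Full Analysis Set. Three further statements in the section matter here:

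- Enrolment: "Assuming that 5% of patients will not qualify for the Full Analysis Set, a total of 62 patients should be enrolled".
- What the loss covers: "The drop-out rate includes patients who experience difficulties in completing questionnaires due to neurocognitive decline during the study period".
- The set: "The Full Analysis Set includes all the subjects who started radiotherapy".

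Section 2.6.1 (Primary Objective) restricts the primary evaluation to patients available for the primary endpoint who have "completed at least 10 questionnaires regarding their symptoms". The same section rules out imputation. The Discussion again treats patients who decline cognitively on study as drop-outs.

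Section 2.4 (Interventions) reports, for the previous trial, that the rate of follow-up ending through the patient's "unavailability was 8.8"%. It offers this as evidence that loss to follow-up is low.

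**The concern.** The sample size argument and the primary analysis refer to different groups of patients. Entry to the Full Analysis Set needs only a start of radiotherapy. Entry to the primary evaluation needs an available endpoint and ten questionnaires. The stated precision should describe the second group, because the AUC and its confidence limit are estimated there, and significance of that AUC is the condition for choosing a cut-off (section 2.6.1).

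The description of the 5% adds to the problem. Failing to enter the Full Analysis Set means not starting radiotherapy. Difficulty with questionnaires because of cognitive decline during the study is a different event, and it normally comes later. Either the 5% is really an allowance for the evaluable set and is attached to the wrong name, or the set definition is not the one intended. A reader cannot tell which, and so cannot tell how many patients the AUC is expected to rest on.

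**Working it through.** **Inputs (section 2.5 unless stated).** Expected AUC A = 0.9; lower limit L = 0.7; two-sided 5% (z = 1.960); assurance 80% (z = 0.842); ratio R = 2.33; 59 required; 5% loss; 62 enrolled. Previous-trial unavailability 8.8% (section 2.4). Pneumonitis rate 37.1% in elderly patients with mean ipsilateral lung dose above 13 Gy (Introduction); that dose threshold is an inclusion criterion here (Table 1).

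**1. Reproducing the 59.** The article cites its method but does not print the formula. Two standard forms reproduce the figure.

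- Simple conservative variance, A(1−A)/m for m positives: m = (1.960 + 0.842)² × 0.9 × 0.1 / 0.2² = 17.66, so 18. Total = 17.66 × 3.33 = 58.8, so 59.
- Binormal variance, V(A)/m with V(A) = 0.0099·exp(−a²/2)·[(5a²+8) + (a²+8)/R] and a = 1.414·z(A), where z(A) is the standard normal quantile of A: V(0.7) = 0.1084 and V(0.9) = 0.0561. Then m = (1.960·√0.1084 + 0.842·√0.0561)² / 0.2² = 17.84, so 18. With 18/41 the assurance is 80.2%.

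The 59 is sound on its own assumptions.

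**2. Reproducing the 62.** 59/0.95 = 62.1, and 62 × 0.95 = 58.9. The gap between 62 and 63 is rounding, but it shows that 62 leaves no margin for any loss above 5%.

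**3. The two sets side by side.**

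| | Full Analysis Set (2.5) | Primary evaluation (2.6.1) |
|---|---|---|
| Entry | radiotherapy started | endpoint available and at least 10 questionnaires |
| 59 required here | yes | not stated |
| Loss allowance | 5% | none stated |
| Removed by on-study cognitive decline | no, once radiotherapy has started | possibly |

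**4. What loss from the evaluable set would do.** The article gives no rate of failing the evaluable-set criteria, so the loss rates below are assumptions. Case rate 30%. Assurance is Φ[(0.2/√(0.09/m)) − 1.960] for the simple form and Φ{[0.2 − 1.960·√(V(0.7)/m)] / √(V(0.9)/m)} for the binormal form.

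| Loss from 62 | Evaluable | Cases | Assurance, simple / binormal | Enrolment to keep 59 |
|---|---|---|---|---|
| 5% | 58.9 | 17.7 | 80.0% / 79.5% | 63 (62.1) |
| 8.8% | 56.5 | 17.0 | 78.4% / 77.4% | 65 (64.7) |
| 10% | 55.8 | 16.7 | 77.9% / 76.7% | 66 (65.6) |
| 15% | 52.7 | 15.8 | 75.5% / 73.7% | 70 (69.4) |
| 20% | 49.6 | 14.9 | 73.0% / 70.3% | 74 (73.75) |

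If 5% never entered the Full Analysis Set and a further 8.8% then left the evaluable set independently, 62 × 0.95 × 0.912 = 53.7 would remain. Assurance would be 76.3% / 74.7%, and 69 enrolled would keep 59.

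**5. Dependence on the case rate.** At 37.1% with 56 evaluable, 56 × 0.371 = 20.8, about 21 cases and 35 non-cases. The binormal form with R = 35/21 gives V(0.7) = 0.1194 and V(0.9) = 0.0598. The assurance is Φ[(0.2 − 1.960 × 0.0754)/0.0534], about 83.6%, which is above the target despite the loss.

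**6. How conservative the planning formula is.** In a simulation with continuous binormal scores, the lower 95% limit from the DeLong standard error exceeded 0.7 in about 96% of samples at 18/41 and about 95% at 17/39–40. With limits on the logit scale the figures were 89% and 87–88%. The real score takes only ten values, so these indicate direction only.

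**The case against.** The strongest reply is that no shortfall is demonstrated, and that stands. A reader might infer from section 2.4 that the 5% contradicts the trial's own 8.8%. It does not. The 8.8% is early end of follow-up through unavailability in another trial, while the 5% is the share who never enter the Full Analysis Set. Nor does early loss always remove a patient from the analysis. A baseline form, six or seven weekly forms and one at the end of radiotherapy (Table 2, section 2.5) would make eight or nine, so one or two telephone visits could bring a patient to ten. Against that, section 2.6.1 also requires the endpoint to be available, and follow-up runs to 24 weeks because pneumonitis can appear as late as week 23. Someone lost early without pneumonitis is not clearly available, and withdrawal or cognitive decline could add to the losses.

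Two further readings do not hold. One is that the trial has only about an even chance of reaching 18 cases (52% with 59 evaluable at a 30% rate). That is true, but 18 is an expected count, so any cohort with a random number of cases behaves this way. The other is that the cited 27.3% rate makes matters worse. That rate comes from the whole retrospective cohort, whereas the same study's 37.1% matches this trial's dose criterion.

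The reply leaves the mismatch of sets and the misfit of the neurocognitive sentence untouched. Neither depends on any loss rate.

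**Conclusion.** The point holds as a matter of definition and is conditional in size. The 59 patients and the 80% assurance are attached to a set that the primary test does not use, and one component of the 5% cannot occur under that set's definition once radiotherapy has begun. The stated properties are therefore not secured for the analysed set. To say that they are not delivered would go further than the article allows, since it gives no rate of failing the evaluable-set criteria.

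At the planned 30% case rate, and assuming all of an 8.8% loss falls on the evaluable set, assurance drops by about two points, to 77–78%. At the 37.1% rate it stays near 84%. Both figures rest on formulas that reproduce the stated 59, not on a printed one, and the simulation suggests that such formulas understate the true assurance. The arithmetic behind 59 and 62 is not in question. This should be corrected, but it does not threaten the trial.

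**What to change.** In sections 2.5 and 2.6.1:

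- Name one primary analysis set and use that name for the 59, the loss allowance and the AUC analysis.
- Define the loss allowance as the proportion failing that set's criteria (endpoint availability and ten questionnaires), with its basis. Enrolment is then 59/(1−d), where d is that proportion.
- Correct the neurocognitive sentence so that it refers to the evaluable set, or change the definition of the Full Analysis Set. Align the Discussion with the choice.
- If enrolment stays at 62, state the expected evaluable number and the assurance over a range of loss rates (for example 5% to 20%) and at both the 30% and the 37.1% case rate.

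The cost is a few sentences and a short recalculation. No additional patients are needed if the figures are restated for 62. The price is that the stated assurance may be slightly less favourable. If the sponsor prefers to keep 59 evaluable under an assumed 8.8% loss, enrolment would be 65, three more than planned.
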